#### Control condition: TAU group

Patients assigned to this arm will receive standard ICU care and should not participate in other RCT aimed at stimulating cognition and providing relaxation during or after the ICU stay.

Standard ICU care for RGS-ICU and TAU groups is based on the ABCDEF bundle, a set of recommendations to optimize recovery and outcomes in patients with critical illness [28, 29].

### Outcomes

The primary outcome is objective cognition 12 months after ICU discharge assessed with a global cognition index (z-score: mean = 0, standard deviation = 1) established on the basis of previous studies [6–8, 13, 14] and composed of validated neuropsychological measures of attention (Forward Digit Span subtest of the Wechsler Adult Intelligence Scale-IV, WAIS-IV), working memory (Backward Digit Span subtest of the WAIS-IV), learning/memory (Rey Auditory Verbal Learning Test, RAVLT), executive function (Trail Making Test, TMT; Stroop Color and Word Test, SCWT; FAS verbal phonemic fluency test) and processing speed (Digit Symbol-Coding subtest of the WAIS-IV; Symbol Digit Modalities Test, SDMT) [30–35].

The secondary outcome is the safety of the intervention assessed by considering the number of sessions terminated early due to unsafe events on physiological parameters [19].

Other outcomes are comfort experienced during ICU stay assessed at ICU discharge with the Patient Evaluation of Emotional Comfort Experienced questionnaire (PEECE) (range 0–48) [36], subjective cognition 12 months after ICU discharge assessed with the Perceived Deficits Questionaire-5 (PDQ-5) (range 0–20) [37, 38], anxiety 12 months after ICU discharge assessed with the Generalized Anxiety Disorder-7 questionnaire (GAD-7) (range 0–21) [39, 40], depression 12 months after ICU discharge assessed with the Patient Health Questionnaire-9 (PHQ-9) (range 0–27) [41, 42], PTSD 12 months after ICU discharge assessed with the Treatment-Outcome Post-Traumatic Stress Disorder Scale (TOP-8) (range 0–32) [43, 44], functionality 12 months after ICU discharge assessed with the World Health Organization Disability Assessment Schedule 2.0 (WHODAS 2.0) (range 0–100) [45], and HRQoL 12 months after ICU discharge assessed with the Short-Form Health Survey (SF-12) (range 0–100) [46, 47].

For all outcomes, except for intervention safety which is only evaluated in the RGS-ICU group, the difference between the RGS-ICU and TAU groups will be considered.

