### Objectives and hypotheses

The main objective is to assess whether patients in the intervention group show better objective cognitive performance than patients in the control group three and 12 months after ICU discharge. The secondary objective is to assess whether the cognitive and relaxation protocols of the RGS-ICU platform are safe for patients with critical illness. Other objectives are to explore whether patients in the intervention group show greater comfort during the ICU stay, as well as better outcomes in subjective cognition, mental health (anxiety, depression and PTSD), functionality and HRQoL than patients in the control group three and 12 months after ICU discharge.

The main hypothesis is that patients in the intervention group will show better objective cognitive performance than patients in the control group three and 12 months after ICU discharge. The secondary hypothesis is that the cognitive and relaxation protocols of the RGS-ICU platform will be safe for patients with critical illness. Other hypotheses are that patients in the intervention group will show greater comfort during the ICU stay, as well as better outcomes in subjective cognition, mental health (anxiety, depression and PTSD), functionality and HRQoL than patients in the control group three and 12 months after ICU discharge.

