Patients will be constantly monitored during the intervention as part of standard ICU care. This will provide information on changes in mental status, mobility level and physiological parameters (e.g., peripheral oxygen saturation [SpO2], respiratory rate [RR] and heart rate [HR]), allowing the study staff to adapt the interaction, workload and duration of each session to the type of patient profile in real time. Adverse events (e.g., unsafe physiological parameters, unintentional removal of catheters, endotracheal tubes or tracheostomy cannulas) and tolerability issues (e.g., fatigue, extreme sleepiness, confusion) during the intervention will result in interruption or early termination of the session. Interruption or early termination of a session will not preclude participation in subsequent sessions if safety criteria are met (see “Safety and tolerability data” and “Harms and adverse event reporting” for details).

The intervention will be discontinued if patients voluntarily withdraw consent or, if they have not yet been able to give consent themselves, their authorized representative voluntarily withdraws consent, requests to stop receiving the intervention, are transferred to another ICU or die during ICU stay. At the discretion of the clinical staff, the intervention will also be discontinued if there are changes in the patient's medical condition, such as worsening disease, that make continued participation inadvisable or if there are safety concerns that poses a risk to participants. In the event of discontinuation of the intervention, patients will continue to receive standard ICU care. Participants should not participate in other RCT intended to stimulate cognition and provide relaxation during or after the ICU stay.

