#### Safety and tolerability data

The safety of the intervention will be assessed by considering the number of sessions terminated early due to unsafe events in physiological parameters, analyzing SpO2, RR and HR [19]. The safety analysis will be based on expert consensus criteria for unsafe active mobilization of patients with critical illness on MV: SpO2 < 90%, RR > 35 breaths/minute and HR > 150 beats/minute, all during ≥ 5 min [56]. Out-of-range values at the start of the session or changes > 20% from baseline in any physiological parameter will also be considered unsafe events requiring that the session not be started or terminated, respectively. Failure to start a session or early termination of a session will not preclude participation in subsequent sessions if the safety criteria are met. Safety physiological parameters will be automatically displayed on bedside monitors using advanced continuous monitoring systems as part of standard ICU care. An alarm will be triggered if an unsafe event occurs. Study staff guiding and supervising the sessions will also visually check the stability of physiological parameters to ensure the safety of the intervention and that no avoidable adverse events (e.g., unintentional removal of catheters, endotracheal tubs or tracheostomy cannulas) occur.

The tolerability of the intervention will be assessed by considering the number of completed sessions and the patients' tolerance to the interaction and workload of the cognitive and relaxation protocols. Therefore, the number of interruptions, the cause of the interruption (e.g., fatigue, extreme sleepiness, confusion), as well as the type and difficulty level of the cognitive and relaxation protocols in which the interruption occurred will be recorded.

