#### Statistical methods

Results will be presented as mean (standard deviation) or frequency (%). Depending on whether the data have a normal distribution, parametric or nonparametric statistics will be used. In case of non-normal data, the median (range) will be reported. To compare results between the RGS-ICU and TAU groups over time, intersubject and intrasubject analyses will be performed, adjusting for multiple comparisons when necessary (e.g., Bonferroni correction). More specifically, intention-to-treat and per protocol analyses will be used. To address missing data, a last observation carried forward analysis together with a complete-case analysis will be performed. Where appropriate, analyses will be controlled for age, sex, delirium, invasive MV, type and dose of pharmacological treatment and/or cognitive reserve (CRQ). Effect sizes will be reported for all significant and non-significant data. Statistical significance will be set at *p* < 0.05. Analyses will be performed using the most recent version of the Statistical Package for the Social Sciences (IBM SPSS Statistics for Windows, Armonk, NY: IBM Corp).

To compare sociodemographic and clinical data between the RGS-ICU and TAU groups, an intersubject analysis will be performed. Intervention characteristics (e.g., session duration, protocols performed, etc.), intervention safety (i.e., number of sessions terminated early due to unsafe events on physiological parameters) and intervention tolerability (e.g., fatigue, extreme sleepiness, confusion) in patients assigned to the RGS-ICU group will be analyzed using descriptive statistics. To compare experienced comfort (PEECE) between the RGS-ICU and TAU groups, an intersubject analysis will be performed. To compare cognition (MoCA, WAIS-IV Forward Digit Span, WAIS-IV Backward Digit Span, RAVLT, TMT, SCWT, FAS, WAIS-IV Digit Symbol-Coding, SDMT and PDQ-5), mental health (GAD-7, PHQ-9 and TOP-8), functionality (WHODAS 2.0) and HRQoL (SF-12) between the RGS-ICU and TAU groups over time, intersubject and intrasubject analyses will be used.

Other analyses will include comparison of changes in the intensity of dyspnea, pain, worry and sadness (VAS) before and after each session in patients assigned to the RGS-ICU group. To this aim, an intrasubject analysis will be used.

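### The safety outcome counts terminated sessions, with no patient-level measure or denominator, although the safety hypothesis is about patients

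*Protocol article*

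**What the plan says.** The Objectives and hypotheses section frames the safety question in terms of patients: "The secondary hypothesis is that the cognitive and relaxation protocols of the RGS-ICU platform will be safe for patients with critical illness". The Outcomes section measures it in sessions, "assessed by considering the number of sessions terminated early due to unsafe events on physiological parameters", and the section on safety and tolerability data repeats the definition: "The safety of the intervention will be assessed by considering the number of sessions terminated early due to unsafe events in physiological parameters". There is no comparator, because Outcomes sets the between-group contrast for everything "except for intervention safety which is only evaluated in the RGS-ICU group". Statistical methods adds only that safety "in patients assigned to the RGS-ICU group will be analyzed using descriptive statistics". No denominator is given, and no count of affected patients is part of the outcome.

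Three further provisions bear on what the count contains:

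- The section on the experimental condition lets a patient return after an event: "Interruption or early termination of a session will not preclude participation in subsequent sessions if safety criteria are met".
- The same section provides for stopping for good. It lets clinical staff withdraw the intervention permanently when a patient's illness gets worse, and it names a second ground: "or if there are safety concerns that poses a risk to participants".
- The section on safety and tolerability data classes out-of-range values at the start of a session as unsafe events. The consequence is that the session is not started.

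The section on additional variables (Table 4) records the number of and reasons for terminations for each session. The section on harms has adverse events collected and analysed for all participants.

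**The concern.** The unit of the outcome does not match the unit of the claim. A clinician who reads that the intervention was safe wants to know what share of patients had an unsafe event or had to be taken off it. The number of terminated sessions does not determine that share, because sessions are nested within patients and one patient may contribute several terminations or none.

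The count is also incomplete. A permanent stop for a safety concern that is decided between sessions adds nothing to it, and any permanent stop ends that patient's further exposure. A session withheld because of unsafe starting values was never begun, so it cannot have been terminated early.

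At stake is the wording of the safety conclusion. With about 40 patients in the evaluated arm, even an event-free result leaves a sizeable per-patient risk that the data cannot exclude. A bare session count gives the reader no sight of that limit.

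**Working it through.** The protocol states no expected event rate, threshold or denominator for safety, so there is no safety figure to reproduce. Its sample size calculation concerns cognition. The inputs are 40 patients planned in the RGS-ICU arm (sample size section) and daily sessions until ICU discharge or 28 days (participant timeline). Event numbers and sessions per patient below are assumptions for illustration.

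**1. One count, many patient risks.** Let the count be the sum over patients of their terminated sessions. Suppose it is 8. Return after a termination is allowed and the window runs up to 28 days, so all 8 could belong to one patient or to eight.

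- Fewest patients: 1/40 = 2.5%.
- Most patients: 8/40 = 20%.

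The reported outcome is 8 in both cases.

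**2. What enters the count.** Four possible courses under the protocol's own provisions:

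| Course of one patient | Added to the count |
|---|---|
| One session terminated as unsafe, patient continues | 1 |
| Terminated on three separate days, then permanently discontinued for safety | 3 |
| Permanently discontinued for safety between sessions, none terminated | 0 |
| Sessions not started because of unsafe values, none terminated | 0 |

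The second patient weighs three times as much as the first. The third and fourth do not appear at all.

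**3. What a patient-level summary would show.** Exact (Clopper-Pearson) two-sided 95% limits:

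- 0 of 40: upper limit = 1 − 0.025^(1/40) = 8.8%.
- 4 of 40: 10%, interval 2.8% to 23.7%.
- 0 of 34, if only 34 patients started a session (assumed): upper limit = 1 − 0.025^(1/34) = 10.3%.

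**4. Would a session denominator alone be enough?** Suppose 4 of 40 patients are stopped for safety at their first session and the other 36 each have m uneventful sessions. Sessions started = 4 + 36m.

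- m = 5: 4/184 = 2.2%.
- m = 10: 4/364 = 1.1%.
- m = 20: 4/724 = 0.6%.

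The patient risk is 4/40 = 10% throughout. The protocol does not propose this rate. The step shows only that dividing by sessions would not replace a count of patients.

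**The case against.** Several stronger readings are tempting, and the document does not support them.

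- **A patient taken off for safety adds at most one event.** A reader might infer this from the discontinuation provision. It does not follow, because terminated sessions do not bar later ones and several may precede a permanent stop.
- **Safe sessions from long-stay patients dilute the outcome.** A raw count does not change when safe sessions are added. The rates in step 4 use a denominator that the protocol does not state; in that example the protocol's own outcome would be 4, which equals the number of affected patients.
- **Per-patient risk is hidden.** It is absent from the outcome, but it can be derived from the per-session records, and adverse events are to be analysed for all participants.

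It can also be said that denominators and intervals are normally left to an analysis plan, and that descriptive statistics do not rule out counting patients. This stands for the choice of interval. It does not stand for the outcome itself, because the article states what is counted, and that is sessions.

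Two more objections are fair. The 8.8% limit comes from having 40 patients, not from the unit of count, and the Discussion already grants that outcomes other than the primary may be underpowered. The patient-level summary does not remove that limit; it makes it visible. Further, with one arm evaluated, worsening critical illness cannot be attributed to the intervention. Discontinuation for worsening disease should therefore not be read as a safety event merely because it is listed next to safety concerns.

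Finally, the protocol cites an earlier proof-of-concept study for this measure. Keeping the session count as a supporting figure preserves any comparison with it.

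**Conclusion.** The concern holds as a mismatch between a stated outcome and the question it is meant to answer. The only secondary outcome is a session count without a denominator or a patient-level measure. It mixes repeat with single events and omits permanent safety discontinuations and sessions not started for unsafe values. One and the same count of 8 is compatible with a patient risk of 2.5% to 20%, taking 40 patients. An event-free result in 40 patients would still leave an upper limit of 8.8%.

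These figures rest on 40 patients starting at least one session and on assumed event numbers; the protocol gives neither an event rate nor sessions per patient. Nothing here shows that the intervention is unsafe, or that the count must understate risk: with repeat events in a few patients, it exceeds the number affected. The change should be made, since the data are largely at hand and the safety conclusion depends on it.

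**What to change.** In Outcomes and Statistical methods, add as the main safety summary the number and percentage of RGS-ICU patients with at least one started session who had either of the following, each also shown separately, with an exact 95% CI:

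- at least one session terminated for an unsafe event;
- permanent discontinuation of the intervention for a safety concern.

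State the upper confidence limit in the safety conclusion. Keep the session count as support, expressed per 100 sessions started with an interval that allows for clustering by patient. Report the number of sessions not started because of unsafe values.

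This changes reporting only; no clinical rule is altered. Terminations and their reasons are already logged for each session. The reason for each permanent discontinuation and each session not started must be recorded in a countable form. The cost is a few lines of text, slightly more analysis, and a headline figure that will look less favourable than a session count.

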### Trial design

A two-arm, parallel group, open-label, superiority RCT with a 1:1 allocation ratio has been designed to evaluate the efficacy and safety of receiving cognitive stimulation and relaxation as an adjunct to standard ICU care (experimental [RGS-ICU] condition) compared with receiving standard ICU care alone (control [treatment as usual, TAU] condition).

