**Intervention (RGS-ICU group only)**					
Cognitive stimulation and relaxation		x	x	x	x
Mobility level of the upper extremities^a^		x	x	x	x
Physiological parameters (SpO2, RR, HR)^b^		x	x	x	x

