#### Harms and adverse event reporting

Previous studies have shown that VR-based cognitive and relaxation interventions can be used safely in the ICU, even in patients with invasive MV [13, 19, 20]. Adverse events (e.g., unsafe physiological parameters, unintentional removal of catheters, endotracheal tubes, tracheostomy cannulas), whether or not related to the use of the RGS-ICU platform, will be collected and analyzed for all participants. No reason for interruption or suspension of the trial is foreseen. However, following the European Commission guidelines on the collection, verification and reporting of adverse events arising from clinical trials [63], in the event of a (serious) adverse event that poses a risk to participants or is causally related to the use of the RGS-ICU platform, the principal investigator may interrupt and/or suspend the trial, and the ethics committee and other relevant parties will be informed.

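### The only secondary outcome, safety, counts physiologically terminated sessions in the RGS-ICU arm alone, so it cannot support a safety comparison with standard care, and it omits other harms that the protocol names

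*Protocol article*

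**What the plan says.** Trial design sets out to evaluate efficacy and safety of the intervention "compared with receiving standard ICU care alone (control [treatment as usual, TAU] condition". Objectives and hypotheses then states: "The secondary hypothesis is that the cognitive and relaxation protocols of the RGS-ICU platform will be safe for patients with critical illness". No threshold or reference rate is attached to it.

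The Outcomes section names one secondary outcome, safety, measured as "the number of sessions terminated early due to unsafe events on physiological parameters". All other outcomes are compared between the groups, "except for intervention safety which is only evaluated in the RGS-ICU group". Statistical methods follows this: safety and tolerability are described in the RGS-ICU group.

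Safety and tolerability data defines the events. It gives absolute limits for SpO2, respiratory rate and heart rate, sustained for at least 5 minutes. It adds that out-of-range values at the start of a session, or "changes > 20% from baseline in any physiological parameter will also be considered unsafe events", and that in these cases the session is not started or is ended, respectively.

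Harms and adverse event reporting is wider. It gives unsafe physiological parameters and unintentional removal of catheters, tubes and cannulas as examples of adverse events, which, "whether or not related to the use of the RGS-ICU platform, will be collected and analyzed for all participants". Table 2 lists SpO2, respiratory rate and heart rate in the block headed "Intervention (RGS-ICU group only", with a footnote saying that they are monitored automatically as part of standard ICU care.

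**The concern.** The aim is comparative, but the outcome meant to address it has no comparator. Critically ill patients also have physiological excursions outside sessions. A count from the treated arm alone cannot separate what the sessions cause from what would have happened anyway.

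The outcome is also narrow. Device removals are among the harms that the protocol itself expects might occur during a session, yet they do not enter the secondary outcome. A session that is not started because values are already out of range involves an unsafe event by the protocol's own definition, but it cannot be counted as terminated early.

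At stake is the safety conclusion. The trial could report on its only secondary outcome without having compared harm between the arms. The wider adverse-event data would stand outside the outcome and hypothesis that they bear on most directly.

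**Working it through.** The protocol gives no safety figure to reproduce. The check is mainly a comparison of passages, followed by some arithmetic for scale.

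**1. Outcome against aim.** The aim (Trial design) compares RGS-ICU with standard care. The outcome (Outcomes, Statistical methods) is described in RGS-ICU only. No reference rate or acceptance limit replaces the missing comparator, so no value of the count would confirm or refute the hypothesis.

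**2. What the outcome captures.**

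| Event the protocol names | Where | In the secondary outcome? |
|---|---|---|
| Session ended early for SpO2, respiratory rate or heart rate | Safety and tolerability data | Yes |
| Session not started, values out of range | Safety and tolerability data | No |
| Unintentional device removal | Experimental condition; Harms | No |
| Any adverse event in TAU | Harms | No |

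**3. Which arm has physiological events.** The harms section includes them for all participants. Table 2 lists the parameters under RGS-ICU only, and Statistical methods names a safety analysis in that arm only. Read together, these leave it unclear whether unsafe physiological parameters in TAU will be recorded as events and analysed.

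**4. One count, two kinds of criterion.** The starting values here are illustrative assumptions. A rise of more than 20% is reached:
- from a respiratory rate of 20, above 20 × 1.2 = 24 (absolute limit 35);
- from a heart rate of 80, above 80 × 1.2 = 96 (absolute limit 150).

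For SpO2 the order reverses: a fall of more than 20% from 98% means below 98 × 0.8 = 78.4%, well past the 90% limit. The relative criterion carries no direction, so a fall in heart rate or respiratory rate counts as well. A pooled total therefore mixes events of very different kinds. This is a reason to report them separately and does not bear on the clinical rule itself.

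**5. What a by-arm comparison could show with 40 per arm** (Sample size section). For assumed proportions of patients with an event, p1 and p2, and n = 40 per arm:

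power = Φ[(|p1 − p2| − 1.96 × SE0) / SE1], where SE0 = √[p̄(1 − p̄) × 2/n] and SE1 = √[p1(1 − p1)/n + p2(1 − p2)/n].

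With p1 = 0.05 and p2 = 0.279: p̄ = 0.1645, SE0 = √(0.1645 × 0.8355 × 0.05) = 0.0829, and SE1 = √(0.00119 + 0.00503) = 0.0788. Then (0.229 − 0.1625)/0.0788 = 0.84, so power is 0.80. The same calculation gives 80% power for about 22% against 2%, 36% against 10%, and 49% against 20%.

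For one arm with no affected patient among 40, the one-sided 95% upper bound is 1 − 0.05^(1/40) = 7.2%.

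**The case against.** The strongest reply is that terminated sessions can exist only where there are sessions. The Outcomes section restricts that one measure, and the harms section describes a separate, wider collection in both arms. Both can be true. This is correct. A reader might infer that the Outcomes section flatly contradicts the harms section, or that the trial will have no safety data from TAU. The documents support neither reading: the harms section promises adverse events in both arms, device removals included. The conflict is narrower. It lies between that promise for unsafe physiological parameters and what Table 2 and Statistical methods assign to RGS-ICU alone.

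It can also be said that Table 2's block lists session procedures, that its footnote places the monitoring within standard care, and that the table has no adverse-event row for either arm. That weakens any claim that TAU events will go unrecorded. It does not settle whether they will be analysed.

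Denominators and table layouts are often left to an analysis plan, and session logs that could supply the denominator are planned. That also stands, but limiting the secondary outcome to one arm and one kind of event is something the article states outright.

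A reader might go further and estimate how many unsafe sessions background fluctuation alone would produce. The documents give neither sessions per patient nor a spontaneous event rate, so no such figure can be supported.

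**Conclusion.** The point holds in a limited form. As defined, the only secondary outcome cannot answer the comparative safety aim or support the safety hypothesis, and it misses two kinds of event that the protocol itself treats as adverse or unsafe. One real inconsistency needs reconciling: unsafe physiological parameters are promised for all participants in the harms section, but are placed in RGS-ICU only by Table 2 and Statistical methods.

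This does not affect the primary outcome. The comparator data are largely promised already and are simply not tied to the outcome. No effect on the result can be sized from the documents. The detectable differences shown rest on assumed event rates and on 40 patients per arm contributing. They mean that a by-arm comparison would be an estimate with a wide interval, and that a null result would not demonstrate safety. The change is worth making because it alters what the trial can conclude about safety.

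**What to change.** - Keep the count of terminated sessions as a descriptive RGS-ICU measure. Report it per session started and per patient, show sessions not started separately, and split events by parameter, direction and criterion (absolute limit or change above 20%).
- Amend Outcomes and Statistical methods so that the secondary safety outcome also includes the adverse events of the harms section, device removals among them. Record them with the same definition in both arms and report them by arm as estimates with confidence intervals. The definition of a physiological event must be one that can be applied in TAU, where there is no session start to serve as baseline.
- Reconcile Table 2 with the harms section, so that it is clear what is recorded in TAU.

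The cost is small: the adverse events are already due to be collected in both arms, so the main addition is one table, with wide intervals at about 40 per arm. Monitoring windows in TAU matched to session times would give a closer comparison, but they are a new procedure whose workload the documents do not allow one to judge. They are optional. The clinical termination rule is left to the clinicians.
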